### Procedure and assessments

As we prepared the current study as a pilot study, the number of families included will be limited. Therefore, it is important to enhance statistical power by applying five repeated assessments (t1 to t5) for the quantitative data: at pre-waiting period, pre-treatment, prior to phase 3, post-treatment, and prior to the booster session. Online and paper and pencil questionnaires will be administered. The qualitative data will be collected after the booster session (t6). The spirit schedule of enrolment, intervention, and assessments is depicted in Fig 1. Siblings will not participate in the assessments.

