**Fig 1 pone.0287472.g001:**
[figure not shown]
Spirit schedule of enrolment, intervention, and assessment. t1 = pre-waiting period; t2 = pre-EFFT; t3 = pre-phase 3 of EFFT; t4 = post-EFFT; t5 = pre-booster session EFFT; t6 post-booster session EFFT. ARE: Accessibility, Responsiveness, Emotional Engagement questionnaire; CSI-4; Couple Satisfaction Index; ECR-RS: Experiences in Close Relationships—Relationship Structures questionnaire; EFFT: Emotionally Focused Family Therapy; RDS: Relationship Dynamics Scale; SEPTI-TS: Self-Efficacy for Parenting Tasks Index Toddler Scale; SDQ: Strengths and Difficulties Questionnaire.

Two measures will be taken to safeguard response to the assessments. First, to guarantee response to the pre-waiting period assessment, the therapist instructs the family during the telephone screening that treatment will start two months from the date the pre-waiting period questionnaires are completed. Second, to make a 100% response rate to the other assessments probable, respondents will gather in the therapist’s room 20 minutes prior to the specific session to complete the questionnaires. The therapist will check that parents and the adolescent complete the questionnaires on their own. Completed questionnaires will be put in an envelope by the therapist which will be sealed by the adolescent in front of the others to guarantee anonymity.

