**Adolescent’s complaints** will be assessed with the Strengths and Difficulties Questionnaire (SDQ) [27]. We will administer the version for children aged 4−17 years to be completed by the adolescent, and the parent version for the parents. We will use the total score, labeled ‘Total difficulties’, which is made up of 20 items and has a Cronbach’s of 0.81 [28]. Optional in low-risk or general population samples is splitting Total difficulties into two subscales, namely Internalizing problems (example items are ‘Many fears, easily scared’ and ‘Rather solitary, tends to play alone’) and Externalizing problems (‘Restless, overactive’ and ‘Often has temper tantrums or hot tempers’) which have a Cronbach’s alpha of 0.73 and 0.78, respectively [29].

The main questions for the evaluation of the feasibility of EFFT are: (1) How do family members evaluate (specific phases of) EFFT?, and (2) What can we learn from their experiences? These questions will be explored in several ways. First, semi-structured interviews will take place after the booster session, with the adolescent being interviewed separately from his or her parents. These semi-structured interviews will last approximately 30 minutes. Open-ended questions will be posed based on a topics list. This list is the result of discussion within the research group. The topics list contains sections with questions about: (1) what motivated the family to seek help, (2) the effects of the therapy they experienced, (3) how the therapist was perceived, (4) their experiences during each therapy phase, (5) how they would rate the therapy, and (6) suggestions for improvement of the therapy. The researchers (DM and TM) who will conduct the interviews are trained in interviewing clients for qualitative research. Further, treatment attendance rates of the family members will be registered. Finally, feasibility of EFFT from the perspective of the therapists will be addressed during a panel discussion at the end of the project.

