### Statistical analyses

As scores are not independent *within* respondents (repeated measurements) and *between* respondents (three dyads: mother and the adolescent, father and the adolescent, and the parents as partners) multi-level analyses are preferred. However, concerning multilevel models with three levels no agreed upon power analyses are available. Therefore, we estimated study power based on a repeated measurements ANOVA with GPower 3.1.9.7 [30]. We anticipate an effect size of *d* = 0.7 which is based on effect sizes obtained by Attachment-Based Family Therapy, which is akin to EFFT (i.e., *d* = .97 [31] and *d* = 1.08 [32]), and the average effect size we obtained with a Couple relationship Education course based on EFT (i.e., *d* = 0.6 [24]). We computed the required sample size to detect this effect size of *d* = 0.7 with a power of .8 an alpha of .05 and a correction for sphericity of e = .5. It was calculated we would need *n* = 20 families. This is a conservative power-estimation based on the number of families as if we only had one person in each family reporting on the outcome measures. However, as several of our outcomes are dyadic by nature (e.g., outcomes regarding interaction patterns between mother and the adolescent, father and the adolescent, and father and mother as partners) the actual power will be higher as the number of individuals will be twice as high for these outcomes.

Following the power analysis we first plan to run a repeated measurements ANOVA to test our main hypothesis concerning change during treatment plus follow-up on the primary outcome. Subsequently, Linear Mixed Models (LMM) in SPSS will be applied with repeated measurements (level 1) nested within respondents (level 2) and, depending on the specific outcome, respondents nested within the dyad of interest (level 3) [33]. In this way we will be able to assess change over time. An advantage of LMM is the possibility to use cases with partial missing data. To adjust for interdependence of the repeated measurements, the AR1 covariance structure will be applied, and to adjust for interdependence of respondents, we will include an intercept at level 3. When results of the multilevel model converge with the repeated measures ANOVA, trust in the robustness of findings will be enhanced.

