We will examine change during the waiting period (comparison of pre-treatment versus pre-waiting period assessments), change during treatment (post-treatment versus pre-treatment assessments), change during follow-up (booster session versus post-treatment assessments), and change during the whole study period (follow-up versus pre-waiting period assessments). We will compute effect sizes (Cohen’s *d*s) using, per comparison, the estimated marginal means, and the pooled standard deviations of the corresponding raw means [34]. Effect sizes will be interpreted as small when Cohen’s *d* is 0.35 or below, moderate when 0.36−0.65, and large when 0.66 or higher. [35]. To evaluate missingness at random, we will apply pattern-mixture models for the dependent variables [36].

The feasibility of EFFT will be evaluated with multiple methods. First, the widely used MAXQDA software will be applied for the qualitative analyses of the semi-structured interviews. We will follow the steps described by Boeije [37]. for inductive thematic analysis. This starts with open coding: fragments relevant to answering the main question will be labeled. Then, several rounds of axial coding will take place where emerging themes within and between participants will be labeled. Finally, the emergent themes will be integrated into an exhaustive representation that describes the overall experience of the families. Second, treatment attendance based upon registrations will be calculated. Finally, treatment adherence will be evaluated by calculating the extent to which the treatment protocol has been executed by the therapists based on ratings by independent raters.

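### Families who stop EFFT early have no stated route to later questionnaires or to an interview, so the first test of the main hypothesis and the interview findings may reflect completers only

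*Protocol article*

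**What the plan says.** **Timing of questionnaires.** The five quantitative assessments fall "at pre-waiting period, pre-treatment, prior to phase 3, post-treatment, and prior to the booster session" (Procedure and assessments). The last three are defined by progress through therapy.

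**Place of completion.** For every assessment after t1, respondents come to the therapist's practice "20 minutes prior to the specific session to complete the questionnaires" (Procedure and assessments, text after Fig 1). The stated purpose is "to make a 100% response rate to the other assessments probable". The same section says "Online and paper and pencil questionnaires will be administered", but does not link the online form to families who have stopped.

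**Interviews.** Under Instruments, "semi-structured interviews will take place after the booster session, with the adolescent being interviewed separately from his or her parents". The family's rating of the therapy is one section of that interview's topics list. Two other feasibility sources do not depend on reaching the booster: registered attendance, and a therapist panel at the end of the project.

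**Analysis.** Statistical analyses tests the main hypothesis on the primary outcome first with a repeated measures ANOVA, then with a linear mixed model (LMM). On the LMM it notes: "An advantage of LMM is the possibility to use cases with partial missing data". It adds: "To evaluate missingness at random, we will apply pattern-mixture models for the dependent variables". Effect sizes use estimated marginal means.

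**The concern.** The in-room procedure protects response only among families who attend. In a first test of a 16 to 21 session treatment, whether families attend to the end is itself a feasibility question, so full attendance cannot be presumed when data collection is designed.

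Two results are exposed. The first is the ANOVA, which in its standard form uses only families with every required wave. The second is the interview material, which the Introduction makes the basis for evaluating feasibility and finding points to improve. Families who left because a phase did not suit them could say most about this, and under the stated schedule they are not asked. Data not collected at the time cannot be recovered by later analysis.

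**Working it through.** **1. What each kind of family supplies under the stated procedure**

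| Family | Questionnaires | In standard ANOVA over treatment and follow-up | In LMM | Interview |
|---|---|---|---|---|
| Stops in phase 1 or 2 | t1, t2 | no | yes, two pre-treatment waves | no |
| Stops in phase 3 or 4 | t1 to t3 | no | yes, three waves | no |
| Finishes, misses the booster | t1 to t4 | no | yes, four waves | no |
| Attends the booster | t1 to t5 | yes | yes | yes |

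A family that stops in phase 1 or 2 has nothing measured after treatment starts. For that family the LMM can lean only on t1 and t2.

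**2. The plan's own sample size**

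Inputs from Statistical analyses: d = 0.7 (f = d/2 = 0.35), power 0.80, alpha 0.05, sphericity correction 0.5, n = 20. The number of occasions m and their correlation rho are not stated; I assume m = 4 (t2 to t5) and rho = 0.5.

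- Noncentrality: f² × N × m × 0.5 / (1 − rho) = 0.1225 × 20 × 4 × 0.5 / 0.5 = 9.8
- Degrees of freedom: 3 × 0.5 = 1.5 and 19 × 3 × 0.5 = 28.5
- Power: 0.805, so N = 20 reproduces. With m = 5 the answer is 18, with m = 3 it is 24.

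The article states no allowance for dropout. Under assumed rates:

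| Dropout | Complete families of 20 | ANOVA power (m = 4, rho = 0.5) | Enrolment for 20 complete, 20/(1 − q) rounded up |
|---|---|---|---|
| 10% | 18 | 0.76 | 23 |
| 20% | 16 | 0.70 | 25 |
| 30% | 14 | 0.63 | 29 |

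**3. Possible bias in a completer analysis**

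Let completers improve by 0.7, stoppers by s, and let q be the share who stop. The all-family effect is 0.7(1 − q) + qs, and the overstatement is q(0.7 − s). Both q and s are assumptions.

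| q | All-family d, s = 0 | Overstatement | All-family d, s = 0.35 | Overstatement |
|---|---|---|---|---|
| 10% | 0.63 | 0.07 | 0.665 | 0.035 |
| 20% | 0.56 | 0.14 | 0.63 | 0.07 |
| 30% | 0.49 | 0.21 | 0.595 | 0.105 |

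**4. How far a likelihood model helps**

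A large-sample simulation used four occasions, AR(1) correlation 0.6, a true t2 to t4 change of −0.70 SD (negative is improvement), 20% dropout after t3, and two strengths of dependence.

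| Stopping depends on | Completers show | Likelihood model shows |
|---|---|---|
| change already observed at t3 (missing at random) | −0.81 to −0.88 | −0.70 |
| later, unobserved change (not at random) | −0.91 to −1.01 | −0.81 to −0.88 |

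The likelihood model removes the bias in the first case and only part of it in the second. Every simulated stopper had a t3 value; families who stop in phase 1 or 2 would not.

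**The case against.** **Families who stop are not lost from all results.** A reader might infer that they drop out of both outcome and feasibility findings. The documents do not support that. Their completed waves stay in the LMM, attendance is registered for everyone, and the therapist panel can discuss them. This stands. But attendance shows that a family stopped without its own account of why, and the panel gives the therapists' view.

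**The LMM does not need dropout to be unrelated to outcome.** It needs missingness at random, so stopping may depend on observed scores. This also stands, as the simulation shows. The planned effect sizes use estimated marginal means, which read most naturally as LMM output, so the overstatement in step 3 applies to a completer analysis such as the ANOVA and not directly to the reported d.

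**Pattern-mixture models are planned.** Their stated use is to examine missingness at random, not to repair bias, so it is no criticism that they cannot restore unseen outcomes. With 15 to 20 families, finely split dropout patterns would be very small. Pooling to completer versus non-completer is possible; 20% of 20 is 4 families.

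**An article condenses.** Follow-up of missed assessments may sit in a fuller protocol, and online forms exist. This carries some weight. However, the article does more than stay silent: it fixes in-session completion for all assessments after t1 and puts the interviews after the booster. Followed as written, that gives completer-only interviews and a completer-only first test.

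**Conclusion.** The point holds in conditional form. If families discontinue for reasons tied to outcome or acceptability, the ANOVA and the interview findings will describe those who stayed. The LMM, attendance records and therapist panel reduce the problem without removing it. The interviews are the part most clearly affected, because no analysis can replace accounts that were never taken.

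The size cannot be fixed from the documents. The range of 0.035 to 0.21 SD rests on assumed dropout of 10 to 30%, completers at d = 0.7, stoppers at 0 or 0.35, and a pure completer estimate. A reader might infer that the reported effect and acceptability are bound to be overstated. That does not follow: no dropout rate is given, dropout may prove small or unrelated to outcome, and the LMM is unbiased under missing at random. The change is worth making because it is inexpensive and must be in place when a family stops.

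**What to change.** 1. Keep in-room completion for families who attend. For families who stop or miss the session, send the online questionnaires at the calendar dates when t3, t4 and t5 would have fallen.
2. Offer families who stop the same 30-minute interview, with the same interviewers, at the time of stopping, and analyse it with the others.
3. Make the LMM on all families with a t1 assessment the main analysis, and report the ANOVA as a complete-case check.
4. Keep the pattern-mixture step, pooled to completer versus non-completer. A scenario of no change from t2 may be added if labelled as a sensitivity analysis. It should not replace the pattern-mixture step: it is single imputation, fixes stoppers' change at zero, ignores any gain seen at t3 and understates uncertainty.

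The cost is a few online links and a few extra interviews. Some families who stop will decline; their number should be reported.

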### Instruments

Evaluation of effectiveness of EFFT in this pilot study focuses on the main objectives of the therapy: (1) de-escalation of negative interaction patterns; (2) enhancement of availability and responsiveness of the parents to the adolescent and between the parents as partners; (3) development of secure attachment between the adolescent and the parents and between the parents as partners; and (4) recovery from the adolescent’s psychological complaints that initiated seeking help. Additional outcome measures are: (5) enhancement of relationship satisfaction between the parents as partners; and (6) disciplining of the child by the parents. We opted for brief questionnaires measuring these concepts as several questionnaires will be completed twice during one assessment by the adolescent and/or parents (see below).

**Negative interaction patterns** will be measured by the Relationship Dynamics Scale (RDS) [21], a four item self-report questionnaire. In EFFT de-escalation, or reduction of negative interactions, is a crucial prerequisite for the development of secure attachment. The RDS items tap into escalation, invalidation, negative interpretation, and withdrawal. An example item is ‘Little arguments escalate into ugly fights with accusations, criticisms, name calling, or bring up past hurts.’ The RDS converges with comparable constructs and can predict changes in communication skills caused by interventions [22]. Originally, the RDS was developed for couples; therefore, we reworded the items to make them suitable for adolescent-parent relationships too. In an earlier study (under review) we found for the original version a Cronbach’s alpha of 0.72 for men and 0.74 for women. The RDS will be completed twice per assessment by the adolescent (separately for the relationship with the mother and the father) and by the parents (separately for the relationship with their adolescent and their partner).

**Accessibility and responsiveness** of the attachment figures, identified by Ainsworth as necessary prerequisites for the development of secure attachment, constitute a central treatment focus in EFFT. We will assess both constructs by an abbreviated version of the Accessibility, Responsiveness, Emotional Engagement questionnaire (ARE) [23]. An example item is ‘If I need connection and comfort, he/she will be there for me.’ Items are scored on a 5-point Likert scale ranging from 1 (disagree) to 5 (agree). As the original ARE was devised for partners in a couple relationship, we reworded the items to adapt the scale for parent-adolescent relationships. Cronbach’s alpha for the six-item scale is .90 for men and women, which is obtained from a recalculation of data earlier published [24]. Of note, this concerns the original, not the reworded, version. The parents will complete the ARE for the relationship with their adolescent. The adolescent will complete the ARE two times per assessment (separately for the relationship with the mother and the father).

Discipline may play an important role in family problems as it can be challenging for parents to be emotionally accessible and responsive to the child and discipline the child simultaneously. The Self-Efficacy for Parenting Tasks Index Toddler Scale (SEPTI-TS) [25] is a self-report questionnaire assessing the parents’ ability to discipline their child. The Discipline subscale consists of seven items. An example items is ‘Other parents seem to have more success with setting limits for their children than I do with my child.‘ Cronbach’s alpha is .81 [25]. Only the parents will complete this questionnaire.

**Attachment** will be assessed with the Experiences in Close Relationships—Relationship Structures questionnaire (ECR-RS) [11]. The ECR-RS consists of nine items and two subscales, namely Anxiety about rejection and abandonment (hyperactivation of the attachment system) and Avoidance of intimacy (deactivation). Cronbach’s alphas for Anxiety are 0.90 for men and 0.88 for women, and for Avoidance 0.90 for men and 0.92 respectively [11]. Originally, the ECR-RS was devised for both parent-child relationships and couple relationships. Example items are ‘I usually discuss my problems and concerns with this person‘ and ‘It helps to turn to this person in times of need.‘ ‘This person’ will be substituted by ‘mother’ or ‘father’ for the adolescent or by ‘partner’ for the parents as partners. Since EFFT focuses on enhancing secure attachment between the adolescent and the mother and the father, the adolescent answers the questions twice. The parents complete the questionnaire only once for their relationship with their partner, but not for their relationship with their adolescent as the child is not an attachment figure for the parents.

**Relationship satisfaction** between the parents as partners will be measured with the four items of the Couple Satisfaction Index (CSI-4) [26], a self-report questionnaire. Although relationship satisfaction is not the main treatment target of EFFT, the parental relationship constitutes the nucleus of the family upon which family relations are built. Therefore, it is important to measure satisfaction with the parental couple relationship. An example item is ‘In general, how satisfied are you with your relationship?’ The CSI-4 highly correlates with the Dyadic Adjustment Scale with 0.87 [26]. Cronbach’s alpha is 0.94 [26].

**Adolescent’s complaints** will be assessed with the Strengths and Difficulties Questionnaire (SDQ) [27]. We will administer the version for children aged 4−17 years to be completed by the adolescent, and the parent version for the parents. We will use the total score, labeled ‘Total difficulties’, which is made up of 20 items and has a Cronbach’s of 0.81 [28]. Optional in low-risk or general population samples is splitting Total difficulties into two subscales, namely Internalizing problems (example items are ‘Many fears, easily scared’ and ‘Rather solitary, tends to play alone’) and Externalizing problems (‘Restless, overactive’ and ‘Often has temper tantrums or hot tempers’) which have a Cronbach’s alpha of 0.73 and 0.78, respectively [29].

The main questions for the evaluation of the feasibility of EFFT are: (1) How do family members evaluate (specific phases of) EFFT?, and (2) What can we learn from their experiences? These questions will be explored in several ways. First, semi-structured interviews will take place after the booster session, with the adolescent being interviewed separately from his or her parents. These semi-structured interviews will last approximately 30 minutes. Open-ended questions will be posed based on a topics list. This list is the result of discussion within the research group. The topics list contains sections with questions about: (1) what motivated the family to seek help, (2) the effects of the therapy they experienced, (3) how the therapist was perceived, (4) their experiences during each therapy phase, (5) how they would rate the therapy, and (6) suggestions for improvement of the therapy. The researchers (DM and TM) who will conduct the interviews are trained in interviewing clients for qualitative research. Further, treatment attendance rates of the family members will be registered. Finally, feasibility of EFFT from the perspective of the therapists will be addressed during a panel discussion at the end of the project.

